### Sample size {14}

The incidence of NADCs in the previous studies SMART and ESPRIT in virologically suppressed patients with CD4> 350 and over 40 years old was approximately 0.04% during 5 years of follow-up [27]. An Italian study described an incidence of NADCs of 0.67 per 100 person-years of follow-up [28]. In the CoRIS cohort, with 31.228 person-years of follow-up, a total of 136 NADCs were diagnosed, and the incidence was 0.43 per 100 person-years of follow-up. In a study of lung cancer screening among smokers, the prevalence of lung cancer was 2.03% [29]. For the calculation of the sample size, we have estimated an incidence of cancer diagnosed at an early stage of 2% in in the intervention group and 1% in the control group. With a statistical power of 80% and a loss to follow-up percentage of 20%, it is estimated that for a unilateral contrast it would be necessary to include 2.319 subjects in the exposed group (enhanced intervention) and 2.319 in the unexposed group (standard intervention) (1:1), with a total sample of 4.638 patients.

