## Statistical methods

### Statistical methods for primary and secondary outcomes {20a}

The primary efficacy analysis will be the comparison of the proportion of cancers diagnosed at an early stage (1 and 2) in each group following the principle of intent to screen, defined as patients who accept to participate in the study and sign the informed consent, regardless of whether they are subsequently excluded due to loss of follow-up, non-adherence to study procedures, unwillingness to remain in the study, death, etc. A per protocol analysis including patients who complete the study will also be performed. A sample size of 2319 patients in each group has been calculated (expected incidence of early cancer 2% and 1% in enhanced and conventional groups, respectively; statistic power 80%; losses to follow-up 20%). Missing observations in the variables will be ignored in the analysis.

The secondary efficacy analysis will include the comparison of the incidence of cancer at any stage or unknown stage and the incidence of new cases of cancer diagnosed at stage 1 and 2 related to all new cases of cancer diagnosed.

The secondary safety analysis will compare the number of unnecessary invasive procedures, the rate of adverse events and severe adverse events, and overall mortality and mortality from cancer in both groups.

The secondary cost-utility analysis will be carried out following the recommendations of the guide for the economic evaluation of health technologies in Spain from the perspective of Spanish National Health System. The incremental cost-effectiveness ratio will be calculated, which is a measure of contrast between the increase in costs and the increase in effectiveness between the different screening alternatives compared. Statistical uncertainty will be expressed as the 95% confidence interval. Random samples of 100 patients from each group replaced 10,000 times will be projected on a graph to generate the increase in QALYs (quality-adjusted life year), the increase in costs, and the cost-effectiveness curve.

The analyses will be performed by a statistician blinded to patients’ allocation using the statistical packages SPSS® v.17 or higher, and R® 3.3 or higher. The statistical significance is set at *p* < 0.05.

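### The cost-utility bootstrap draws only 100 patients per arm, so its scatter of incremental costs and QALYs would be about 4.3 to 4.8 times too wide and a curve built from it too flat

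*Protocol article*

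**What the plan says.** The protocol article, Statistical methods for primary and secondary outcomes {20a}, describes a secondary cost-utility analysis from the perspective of the Spanish National Health System, with an incremental cost-effectiveness ratio (ICER). Two consecutive sentences deal with uncertainty. The first reads "Statistical uncertainty will be expressed as the 95% confidence interval". The second fixes the resampling: "Random samples of 100 patients from each group replaced 10,000 times will be projected on a graph to generate the increase in QALYs", and goes on to name the increase in costs and the cost-effectiveness curve as further products.

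The same section gives the arm size: "A sample size of 2319 patients in each group has been calculated". It also says that missing observations will be ignored. Sample size {14} assumes early-cancer rates of "2% in in the intervention group and 1% in the control group" and a 20% loss to follow-up.

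No reason is given for 100 and no rescaling to the arm size is mentioned. Methods for additional analyses {20b} separately plans a probabilistic sensitivity analysis, shown as a cost-effectiveness plane and an acceptability curve.

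**The concern.** The spread of bootstrap replicates depends on how many patients are in each resample. Resampling an arm at its own size imitates repeating the trial. Resampling 100 per arm imitates repeating a 200-patient study with the same patient-level variation. The protocol states the number explicitly, so this is not a detail left to a later document.

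Cost-utility is specific objective 3 in Hypothesis and objectives {7}, and the Discussion says that the trial should help to show whether the programme is cost-effective for public health services. An over-dispersed cloud and a flattened curve could make a clear result, in either direction, look undecided.

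**Working it through.** **Inputs.** Resample size m = 100 per arm and B = 10,000 replicates ({20a}); planned n = 2,319 per arm ({14}, {20a}); loss to follow-up 20% ({14}). I read the resampling sentence as 10,000 resamples drawn with replacement.

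**The plan's own figure.** {14} describes a one-sided comparison of 2% with 1% at 80% power; {20a} sets significance at 0.05. With the pooled two-proportion formula:

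n = [1.645·√(2·0.015·0.985) + 0.842·√(0.02·0.98 + 0.01·0.99)]² / 0.01² = 1,826

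Dividing by 0.8 gives 2,283, which is 1.6% below 2,319, so the planned size is reproduced closely enough to use here. (The two-sided formula without inflation for losses gives exactly 2,319. That does not change this point.)

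**Analysed size.** If everyone contributes, n = 2,319. With 20% lost, 2,319 × 0.8 = 1,855.

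**Inflation of the spread.** For a difference in mean cost or mean QALYs, with patient-level variances s₁² and s₀²:

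- SD of replicates at size m: √((s₁² + s₀²)/m)
- SD of replicates at size n: √((s₁² + s₀²)/n)
- Ratio: √(n/m). The variances cancel, so no cost or QALY data are needed.

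| Analysed per arm | Variance ratio n/m | SD ratio √(n/m) |
|---|---|---|
| 2,319 | 23.19 | 4.82 |
| 1,855 | 18.55 | 4.31 |

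**Number of replicates.** B governs only Monte Carlo noise. With B = 10,000 the relative error of an estimated SD is about 1/√(2 × 10,000) = 0.7%. The wrong spread is therefore estimated precisely.

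**Illustration on assumed data.** The document gives no cost or QALY variances, so these inputs are invented: 2,319 per arm; exponential costs with mean 1,500, plus 300 in the enhanced arm; QALYs about 2.52 and 2.50 with SD 0.5, limited to 0–3; 10,000 replicates.

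| Quantity | m = 100 | m = 2,319 |
|---|---|---|
| SD, incremental cost | 210.2 | 43.9 |
| 95% range, incremental cost | −134 to 689 | 194 to 365 |
| SD, incremental QALYs | 0.0616 | 0.0129 |
| Curve at 20,000 per QALY | 0.58 | 0.82 |
| Curve at 30,000 per QALY | 0.61 | 0.90 |
| Curve at 60,000 per QALY | 0.64 | 0.95 |

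Both SD ratios are 4.8, as the formula predicts. The curve values also follow: 0.90 corresponds to z ≈ 1.30; 1.30/4.82 = 0.27; and Φ(0.27) = 0.61. Only the ratios carry over to the trial. The cost, QALY and curve values depend on the invented inputs.

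**The case against.** The strongest case for the plan has five parts.

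- **The confidence interval.** A reader might infer that the reported 95% interval will be 4.8 times too wide. The two sentences are adjacent, but nothing links the interval to the replicates; it could be computed from the full data by another method. This objection stands. If the interval is computed otherwise, the plot would disagree with it.
- **The curve and the ICER.** A reader might apply the factor of 4.8 to everything. An acceptability curve is a probability at each threshold and has no such width: it is flattened. An ICER is a ratio, so its interval does not scale by a fixed factor. The factor applies only to incremental costs and incremental QALYs.
- **The sensitivity analysis in {20b}.** Its plane and acceptability curve do not depend on the 100-patient draw, so the economic conclusion does not rest on this plot alone. That limits the harm. It does not repair the plot in {20a}, because it addresses uncertain model values and not sampling error between patients.
- **Rare cancers.** At 1% and 2%, 0.99¹⁰⁰ = 37% of control resamples and 0.98¹⁰⁰ = 13% of enhanced resamples would contain no early cancer. It is tempting to treat this as the size of the error. It is only a proxy: the resampling is applied to costs and QALYs, and participants without cancer also incur screening costs.
- **Deliberate small resamples.** Drawing fewer patients than the arm contains can be valid if the spread is rescaled. The text mentions neither rescaling nor a reason for 100, so this does not rescue the sentence.

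**Conclusion.** The sentence is wrong as written for its purpose. Followed literally, it overstates the spread of incremental costs and incremental QALYs by a factor of 4.3 (20% lost) to 4.8 (all 2,319 per arm analysed). Any percentile interval taken from the replicates is widened by about the same factor, and a cost-effectiveness curve built from them is drawn toward 50%.

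This rests on two assumptions: that 100 is the size of each resample, and that no rescaling is applied. It does not depend on the unknown cost and QALY distributions.

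The reach is limited. The error touches a secondary analysis, though one that serves a named objective. The primary outcome and the point estimates of incremental cost, incremental QALYs and the ICER from the full data are untouched. The documents do not support saying that the trial's 95% intervals are wrong, or that the economic evaluation as a whole would be inconclusive.

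**What to change.** Replace the resampling sentence in {20a} with: *In each of 10,000 replicates, participants in each arm are resampled with replacement at the arm's full analysed size, and the plot of incremental costs and QALYs, the cost-effectiveness curve and any bootstrap 95% interval are taken from these replicates.*

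It would help to say at the same time whether the reported 95% interval is the bootstrap interval. Resampling within sex, to mirror the allocation by sex in Sequence generation {16a}, is optional and not needed to correct the error.

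The cost is one sentence and slightly more computing time. No new data are needed, and the change can be made at any point before the economic results are reported.

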### Interim analyses {21b}

Interim analyses for futility, safety, and efficacy are planned every 12 months. The analyses will be performed by an independent data monitoring committee-DMC (an HIV specialist, a statistician, and an oncologist). There are no prespecified rules for stopping the trial. The DMC will review efficacy and safety data at each interim analysis and report to the trial steering committee who will make the final decision to terminate the trial if there are sufficient safety concerns or futility.

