## Oversight and monitoring

### Composition of the coordinating center and trial steering committee {5d}

The steering committee, made up of eight academic investigators, developed the study protocol, will have full access to the interim data, is responsible for the decision to stop the trial, will publish the results, and wrote the manuscript. The committee members will vouch for the accuracy and completeness of the data reported. Endpoint adjudication will be performed by the investigators at the participating centers. The DMC may be asked to evaluate equivocal cases where the assignation of an outcome requires the judgment of an oncologist. Data management will be carried out by the CRO.

Steering Committee: [name], [name], [name], [name], [name], [name], [name] and [name].

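### Yearly efficacy looks have no stated consequence and no boundary, and an investigator steering committee sees the interim data of an open-label trial

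*Protocol article*

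**What the plan says.** All references are to the protocol article.

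- **Interim analyses {21b}.** "Interim analyses for futility, safety, and efficacy are planned every 12 months". The section continues: "There are no prespecified rules for stopping the trial". On reporting: "The DMC will review efficacy and safety data at each interim analysis and report to the trial steering committee". The sentence then turns to that committee, "who will make the final decision to terminate the trial if there are sufficient safety concerns or futility". Efficacy is a listed purpose of each look but not a listed ground for stopping.
- **Statistical methods {20a}.** Significance is set at p < 0.05, with no allowance for repeated looks. The analyses are to be done by a statistician blinded to allocation.
- **Outcomes {12}.** The primary outcome, a new NADC at stage 1 or 2, is compared at 12, 24 and 36 months.
- **Steering committee {5d}.** "The steering committee, made up of eight academic investigators, developed the study protocol". It also "will have full access to the interim data, is responsible for the decision to stop the trial". Endpoints are adjudicated by investigators at the participating centers, and "The DMC may be asked to evaluate equivocal cases where the assignation of an outcome requires the judgment of an oncologist".
- **Blinding {17a}.** The trial is open label.
- **Discussion.** A historical control group may be added after the first interim analysis if judged strictly necessary.

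**The concern.** There are two separate problems.

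**Error rate.** A look at efficacy costs type I error only if something can follow from it: stopping for benefit, or claiming benefit. The article schedules such looks every year, says that no rules govern them, and does not say that they carry no inferential weight. A reader of the final report could not tell whether p < 0.05 was the only chance of success or one of several.

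**Conduct.** The primary endpoint depends on how intensively findings are worked up and how stage is called, by staff who know the allocation. Sharing interim results with trial investigators while follow-up continues can affect both. The option of adding a historical control group after the first interim analysis makes this worse: it is a design change with no rule, open to a committee that may already have seen the comparison.

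**Working it through.** **1. The plan's own sample size, to fix the setting.** Inputs from Sample size {14}: 1% and 2%, one-sided, power 80%, loss 20%. Alpha 0.05 is taken from Statistical methods {20a}.

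n = [z₀.₉₅·√(2·p̄·(1−p̄)) + z₀.₈₀·√(p₁(1−p₁)+p₂(1−p₂))]² / (p₂−p₁)², with p̄ = 0.015

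= [1.645·√0.02955 + 0.842·√0.0295]² / 0.01² = 1,826 per arm.

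1,826 / 0.80 = 2,283, against 2,319 stated, a difference of 1.6%. With 2,319 enrolled, 2,319 × 0.80 ≈ 1,855 per arm are evaluable, giving one-sided power of 80.5% with a single final test.

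**2. Type I error if efficacy is claimed only once, at the end.** Stopping for safety or futility can only remove rejections under the null hypothesis. The overall error is at most 5%.

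**3. Type I error if any look could support a claim at unadjusted 0.05.** The statistics Z₁…Z_K are multivariate normal with correlation √(t_i/t_j) for i < j, and the error is P(at least one Z_k beyond the critical value), with 1.645 one-sided or ±1.96 two-sided. With equal information:

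| Looks, final included | One-sided | Two-sided |
|---|---|---|
| 2 | 8.0% | 8.3% |
| 3 | 10.1% | 10.7% |
| 4 | 11.7% | 12.6% |
| 5 | 13.0% | 14.2% |
| 7 | 15.0% | 16.6% |

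Both columns are shown because the sample size is one-sided and the analysis section does not state sidedness.

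**4. How many looks.** The article gives no number. Three matches the 12-, 24- and 36-month comparisons. Seven follows from the Trial status dates: recruitment from June 2019 to the end of 2022 is 3.5 years, plus 3 years of follow-up is 6.5 years, so looks at years 1 to 6 and a final analysis.

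**5. Sensitivity to unequal information.** With uniform accrual and information proportional to person-years, the seven fractions are 0.048, 0.190, 0.429, 0.702, 0.893, 0.988 and 1. The any-look error is then 16.2% one-sided and 17.7% two-sided. The first look would rest on few events: 0.048 × 3,710 evaluable × 0.015 ≈ 2.7. Simulating binomial events under the null hypothesis (1.0% or 1.5% in both arms) on this calendar gives 14.9–15.9% one-sided and 14.7–15.1% two-sided.

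**6. Cost of a boundary.** O'Brien-Fleming limits with total alpha 0.05, equal information and 80% power for a single test:

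- 3 looks: final nominal p about 0.044 one-sided or 0.045 two-sided; power loss 0.9 or 0.7 points.
- 7 looks: final nominal p about 0.038 or 0.039; power loss 1.6 or 1.3 points.

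**7. Governance.** No arithmetic applies. {21b} describes an independent DMC that runs the looks and reports to the steering committee. {5d} gives that committee full access to the interim data. With the second statement in force, the DMC does not act as a barrier between the comparative results and the people running the trial.

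**The case against.** The strongest reply is that {21b} names only safety concerns and futility as reasons to terminate. On that reading no efficacy stop exists, efficacy is tested once, and the 5% rate holds. This stands as far as it goes: a reader might infer that the trial's error rate is 10.7% or 16.6%, and the article does not support that as a statement of fact. Those figures apply only if a look can lead to an efficacy stop or claim. The reply does not close the matter, because efficacy remains a listed purpose and nothing in the article rules out acting on it.

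Other limits on the point:

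- A reader might infer that steering committee members themselves recruit, screen and adjudicate. {5d} calls them academic investigators and says no more. It also does not say in so many words that the interim data are shown by arm, though a futility decision would ordinarily need that. The concern rests on trial investigators having access, not on their own sites' role.
- A reader might infer that a 12-month futility look has no screening behind it. Table 1 places enhanced-arm liver, anal and cervical tests at month 6, and {21b} does not say when the 12-month clock starts. Judgment-based futility review does not inflate type I error.
- The blinded statistician in {20a} protects the computation. It does not protect work-up or staging by people who know interim results.
- Numerical futility criteria are ordinary DMC charter content, and their absence here is not held against the plan.

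The missing efficacy rule cannot be left to an unseen analysis plan in the same way, because the article states that there are none.

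**Conclusion.** The point holds in two parts. First, the purpose of the yearly efficacy looks is undefined, so control of the error rate depends on an unstated intention. It is at or below 5% if efficacy is claimed only at the end, and about 10–11% (3 looks) to 15–17% (7 looks) if any look can support a stop or claim. The range rests on an assumed number of looks and equal information; calendar-based information moves the seven-look figure only to about 15–18%.

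Second, and independently of alpha, full steering committee access to interim data in an open-label trial, with a stage-based endpoint adjudicated by unblinded site investigators and a historical control option after the first look, exposes conduct and outcome assessment to bias. The documents do not allow that bias to be sized.

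**What to change.** 1. **Interim analyses {21b}: choose one.** Either remove efficacy testing from the interim looks and state that efficacy is tested once, at the end; or keep it with an O'Brien-Fleming-type alpha-spending boundary, total alpha 0.05, and an adjusted final test. The first option costs no power. The second costs about 1 point for 3 looks and up to about 1.6 for 7, starting from 80%.
2. **Interim analyses {21b}: futility.** State that it is non-binding. Leave its criterion and timing to the DMC charter.
3. **Steering committee {5d}.** Keep comparative interim data with the DMC, and have the steering committee receive only a recommendation. Any decision about a historical control group would then be taken without sight of the comparison.

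This needs a short protocol amendment and matching charter text. It requires no new data and no change to participants' care.

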### Methods for additional analyses (e.g., subgroup analyses) {20b}

Subgroup analyses will be performed for: age groups every 5 years, sex, status of smoking, risk group, CD4 range, CD4 nadir, and HIV viral load. Sensitivity analysis will also be performed on the uncertain values of the model, taking the most pessimistic and optimistic assumptions about long-term survival of each tumor. Sensitivity analyses related to internal validity will also be carried out in the following variables: quality of life after positive screening and after the diagnosis of NADCs and radiation-induced cancer deaths. To analyze the generalizability of the results, sensitivity analyzes will be carried out in the operative mortality and in various costs, such as the costs of screening, follow-up LDCT, surgery, chemotherapy, radiotherapy, and management of incidental findings. A sensitivity analysis will also be carried out using an annual discount of 0 and 5%. The sensitivity analyzes will be carried out through a probabilistic sensitivity analysis, and the results will be presented as a dispersion analysis (cost-effectiveness plan) and the acceptability curve.

The same statistical packages SPSS® v.17 or higher, and R® 3.3 or higher will be used to carry with these subgroup analysis. The statistical significance is also set at *p* < 0.05.

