### Eligibility criteria {10}

Inclusion and exclusion criteria for participants:

Inclusion criteria: adult patients ≥ 18 years with confirmed HIV infection and who agree to participate in the study and sign the informed consent.

Exclusion criteria: any active AIDS-defining disease, current or past NADC, life expectancy < 5 years, pregnancy or lactation, patients who refuse to participate in the study, any other criteria that in the judgment of the clinician should prevent the patient to participate in the study.

Eligibility criteria for study centers: Spanish hospitals with HIV/AIDS Unit and Infectious Diseases/HIV (ID/HIV) specialists.

Eligibility criteria for study individuals who will perform the interventions: ID/HIV specialists, radiologists, gynecologists, and surgeons.

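### Subgroup analysis by 5-year age band and six other factors, judged at unadjusted p < 0.05, is too sparse to show who benefits and carries about a 30% risk of a false subgroup claim even with one test per factor

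*Protocol article*

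**What the plan says.** The section on additional analyses {20b} lists the subgroup factors: "age groups every 5 years, sex, status of smoking, risk group, CD4 range, CD4 nadir, and HIV viral load". That is age plus six others. Of these analyses it then says: "The statistical significance is also set at *p* < 0.05". It states no multiplicity adjustment, no interaction test and no exploratory label. It gives neither the number of age bands nor the levels of the other six factors, and it does not say whether arms are compared within each level or the effect is compared across levels.

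Eligibility {10} admits "adult patients ≥ 18 years with confirmed HIV infection" and sets no upper age limit, so the 5-year grouping runs over the whole adult range. The sample size section {14} assumes "an incidence of cancer diagnosed at an early stage of 2% in in the intervention group and 1% in the control group" and arrives at 2,319 per arm, 4,638 in total. No sample size is given for any subgroup.

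**The concern.** Two things are fixed here, and both work against a useful subgroup answer.

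- **Banding.** Few events are expected even in the whole trial. Dividing them among 5-year bands leaves each band with a handful, so a band will usually show nothing and will sometimes show the reverse of the truth.
- **Threshold.** p < 0.05 is the only stated criterion for a subgroup claim, and it is applied to seven factors without adjustment.

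The article says in its background that the trial is meant to inform guidelines on screening in people with HIV, and guideline writers will ask who benefits. A chance positive in one band, or an apparent absence of benefit in another, could be read as an answer to that question.

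**Working it through.** **Inputs.** From {14}: 2% against 1%, 80% power, 20% loss, one-sided test, 2,319 per arm. From {20a} and {20b}: significance level 0.05. Not in the article, so assumed: 8 to 13 age bands of equal size (ten as the worked case), and 2 to 4 levels for each other factor.

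**1. The plan's own figure.** The two-proportion formula without continuity correction, one-sided 5%, 80% power, gives 1,826 per arm. Then 1,826 / 0.8 = 2,283, within 1.6% of 2,319. (The two-sided formula with no allowance for loss gives exactly 2,319.) Both 2,319 and 2,319 × 0.8 = 1,855 per arm are carried forward.

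**2. Events per age band, both arms together.**
- No loss: 2,319 × (0.02 + 0.01) = 69.6 events. Over 8, 10 and 13 bands: 8.7, 7.0 and 5.4.
- After 20% loss: 1,855 × 0.03 = 55.7 events. Over 8, 10 and 13 bands: 7.0, 5.6 and 4.3.

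The range is therefore about 4 to 9. Real events will be uneven across age, and the youngest bands will probably fall below this average.

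**3. Power in one of ten bands (232 per arm, two-sided 5%).**
- SE under the null = √(2 × 0.015 × 0.985 / 232) = 0.01129.
- SE under the alternative = √((0.02 × 0.98 + 0.01 × 0.99) / 232) = 0.01128.
- Power = Φ[(0.01 − 1.96 × 0.01129) / 0.01128] = Φ(−1.07) = 14%.
- Fisher's exact test, by summing the two binomial distributions: 6%.
- Normal approximation after 20% loss (186 per arm): 12%. One-sided: 22% without loss, 20% with it.

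**4. Reversed direction when the effect is the same everywhere.** Take X ~ Bin(232, 0.02) in the enhanced arm and Y ~ Bin(232, 0.01) in the conventional arm. Then P(Y > X) = 13.6%. At least one reversal in ten bands: 1 − (1 − 0.136)^10 = 77%. With 186 per arm it is 81%.

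**5. Chance of at least one false claim at unadjusted 0.05.**
- One test per factor, seven tests treated as independent: 1 − 0.95^7 = 30%.
- Thirteen independent tests give 1 − 0.95^13 = 48.7%, and fourteen give 1 − 0.95^14 = 51.2%. So at least 14 are needed to pass one half.
- If every level were tested separately and there were no effect anywhere, simulation gives the values below. It used 2,319 per arm, a 1.5% event rate in both arms, ten equal age bands plus six factors, and 4,000 runs.

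| Assumed cells | z test | Fisher's exact test |
|---|---|---|
| 22 | 56% | 33% |
| 27 | 65% | 40% |

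Fisher's test gives less because it is far below its nominal level with so few events: about 1.5% in one of ten bands at a 1.5% rate.

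**The case against.** The strongest reply is that the article leaves much of this open. It names factors and a threshold but no test, no levels and no end bands. Interaction tests, cut-points and an exploratory label often sit in an analysis plan that is not shown here. The analyses stand under additional analyses, and nothing calls them confirmatory. All of that is fair, and the absence of those details is not the point. What stands is what the section does fix: 5-year bands, and p < 0.05 for the subgroup analyses.

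A reader might infer that a false subgroup claim is more likely than not. The documents do not support that. It requires a separate test in every level, which {20b} never states, a z-type test rather than an exact one, and no effect in any level. One test per factor gives 30%, and Fisher tests in all 22 to 27 assumed cells stay below one half. If the planned doubling is real, a significant result within a level is not a false positive at all. The relevant error is then a false claim that the effect differs between levels, which brings back the 30%. Nor does {20b} say that subgroups are tested at each of 12, 24 and 36 months, so no further inflation is counted.

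A reader might also say that the bands ignore the ages at which screening starts. That is weak: 5-year bands can have boundaries at 40 and 50, and the intervention description {11a} uses other ages too, such as 21, 30, 64 and 70. The problem is how thin the bands are, not where they are cut.

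**Conclusion.** The point holds in a limited form. Under equal bands and the planned rates, a 5-year age band would hold about 4 to 9 early-stage cancers, with 6% to 14% two-sided power in one of ten bands. At least one band in ten would be expected to reverse direction about 77% of the time by chance alone. No band count in the assumed range rescues this. The unadjusted threshold carries about a 30% risk of at least one false claim with one test per factor, six times the nominal 5%. Testing every level could raise this to about 65% with z tests, or 40% with exact tests, at 27 assumed cells, but that reading is conditional.

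The number of bands, their equal size, the levels of the other factors and the independence of the seven tests are assumptions. The primary analysis, the participants and data collection are unaffected. The case for acting is that a foreseeable misreading can be removed cheaply before the data are analysed.

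**What to change.** In the section on additional analyses {20b}:

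- Replace the 5-year age grouping by age as a continuous term, or by a few broad bands, for example split at 40 and 50, where many of the screening tests begin.
- Assess each of the seven factors by one arm-by-factor interaction test.
- Report the effect in each subgroup with a 95% interval, and label these results exploratory.
- Remove the p < 0.05 rule as the criterion for a subgroup claim.

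The cost is analysis wording only. Sample size, procedures and the primary analysis stay as they are. The downside is coarser age detail and fewer subgroup results that can be reported as significant. Interaction tests will also have low power with about 70 events, which is a further reason to report intervals rather than verdicts.
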